### Patient and public involvement

No formal patient and public involvement (PPI) group was convened for this study; however, phase 1 is a standard protocol used at the HMRU and has been continually developed with PPI for over 10 years. The methodology using a single-lead wearable ECG device and CGM was discussed and reviewed with participants for a previous study investigating the effects of resistance exercise and protein supplementation on sarcopenia in healthy older men (ClinicalTrials.gov Registry: NCT03299972). The PPI consists of informal, non-scripted interviews with members of the public post-study via the UHCW PPI forum. Depending on the results obtained, PPI groups may be approached to discuss non-scientific dissemination.

## Discussion

The primary objective of this observational study is to obtain physiological data from people with T1DM using non-invasive wearable sensors to validate and further develop an AI model for automated detection of hypoglycaemia. The initial model^15^ was developed using data from healthy individuals and the results determined that the personalised classifiers based on deep learning algorithms can reliably perform automatic detection of hypoglycaemic events using features extracted from the ECG waveform recorded with wearable devices. This study is designed to improve the performance and robustness of this AI model for use in a population with T1DM. Additionally, as a secondary outcome, this study will examine impact of lifestyle habits such as exercise, diet and sleep as predictors in the model.

The study will add to the body of evidence evaluating AI for use in the detection of glycaemic events (eg, hypoglycaemia) in free-living conditions. Current efforts in the literature have been limited by small sample sizes,^48^ healthy subject populations^16^ and data originating from highly controlled experimental settings.^49^ This study protocol has been developed to address the gaps of the existing literature. As such, the strengths of this study design are that data are collected from participants with diabetes, both in controlled and free-living settings. An additional strength of this protocol is that it has been designed with non-compliance in mind. The first phase will take place in a metabolic chamber where the activities of the participants and the operation of the wearable sensors are prescriptive and supervised. This enables us to obtain high-quality baseline data. The second phase will take place in free-living conditions where the participants go about their normal daily activities unencumbered by the wearable sensors, providing real-life data. During the free-living phase, a level of non-compliance and variance is desirable in order to determine how our analysis and model work with real-world data. Non-compliance with the protocol will not exclude the participant from inclusion in the analysis. Any deviations from the protocol will be noted. Participation in both phases of the study is not a requirement; therefore, we are likely to obtain different number of samples for each participant. We will take a pragmatic approach and work with the data available at the end of the study. All analyses will report the number of samples used and if excerpts of data have been excluded and for what reason. Our planned analysis will segment the continuous physiological data into smaller excerpts of variable length, yielding a sufficient sample size for the training algorithm to discover relevant features in the data.

A potential limitation of this protocol is that during the free-living phase of the study, participants will be required to extract data from the CGM at least once every 8 hours. They will also have to remove and reattach the ECG device when engaging in water-based activities or exchanging the device for a new fully charged one. This introduces scenarios with the possibility of missing data such as if a CGM scan is missed, the ECG device is not changed when the battery is depleted or it is not correctly activated. To mitigate this, participants will be provided with instructions and a demonstration as well as an information sheet. A member of the research team will also be contactable throughout if further assistance is needed.

To our knowledge, no studies have attempted to develop a glycaemic event detection model for people with T1DM using deep learning with raw single-lead ECG signals. This study is being run complementary and in parallel to another involving paediatrics with T1DM.^50^ In our planned analysis, we will investigate changes in the ECG morphology and other features derived from the ECG signal with respect to glycaemic status. A novel aspect of the analysis will be the inclusion of additional features such as activity levels, mealtimes and composition, and sleep patterns.

Non-invasive monitoring of blood glucose and glycaemic event detection can potentially eliminate the need for finger-pricking. The development of an accurate and robust model for the non-invasive detection of abnormal excursions of blood glucose is pivotal for efficient management of metabolic disorders such as diabetes, drastically reducing discomfort, costs and waste associated with current invasive methods to measure blood glucose concentration. A continuous non-invasive blood glucose monitoring solution could help to overcome barriers and limitations of traditional methods, thereby increasing adherence to self-management protocols leading to improved outcomes, quality of life and reduced incidence of complications.

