## Methods and analysis

### Study setting

This two-phase observational study will be conducted at the Human Metabolism Research Unit (HMRU) and in free-living conditions. During phase 1, the participants attend an inpatient protocol at University Hospital Coventry and Warwickshire (UHCW) in a calorimetry room for up to 36 hours. The calorimetry room is a controlled environment, which allows for precise regulation of parameters such as ambient temperature, air pressure, humidity and subject behaviour enabling us to obtain high-quality baseline ECG and glucose data from the wearable sensors. In phase 2, the same sensors will be used to collect data under free-living conditions, for a period of up to 3 days, during which the participants are free to go about their normal daily activities without restriction. Participants will be asked to complete diaries for daily activity, food intake and sleep.

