### Study protocol

#### Calorimetry room

The participant will stay in the calorimetry room for up to 36 hours, during which there will be set times for meals, light exercise and rest. Meals will be provided with known total energy and macronutrient content. Water will be provided ad libitum. While in the calorimetry room, wearable sensors will record physiological data continuously.

Other activities will be performed during this time, specifically: (a) up to 12 serial blood samples of 30 mL will be obtained from a peripheral venous catheter inserted at the beginning of phase 1 to measure venous glucose and insulin concentration, (b) finger-prick blood samples will be taken periodically for capillary glucose measurements, (c) up to 12 saliva samples will be taken to analyse salivary concentration of cortisol and melatonin, (d) all urine will be collected as voided for protein oxidation analysis, (e) movement and activity will be assessed by motion sensors, (f) simple questionnaires will be used to measure food intake and activity as well as subjective aspects such as appetite, satiety and wellness, and (g) daytime blood pressure will be monitored using an ambulatory blood pressure monitor (hourly readings).

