### Devices

#### Continuous glucose monitoring

Continuous glucose levels will be measured using a FreeStyle Libre 2 flash glucose monitoring system, which can be worn for up to 14 days. Although the sensor is sampling continuously, the glucose concentration is reported in 15-minute intervals. The sensor can store data for a period of 8 hours. As such, data will be extracted at regular intervals using a smartphone preconfigured with the companion application. The sensor is water resistant and can be used while bathing, showering, swimming or exercising, and is worn on the back of the upper arm. The device has been evaluated for accuracy and user experience and found to have been generally well received by patients with T1DM who used it for 10–14 days.^29^

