### Data analysis and modelling

#### Data processing

The effect of glycaemic events on the ECG signals will be examined. It is anticipated that ECG signals will be affected by noise and artefacts due to body movement or heavy respiration. Therefore, we will apply preprocessing methods such as baseline wander removal to the raw signal to remove low-frequency noise. We will then identify individual heartbeats in the ECG and detect fiducial points using our ECG segmentation tool,^31^ which has been used in a recent study for cardiovascular disease detection.^32^ Heartbeats will then be grouped into 15-minute excerpts, corresponding to the sampling of the CGM, and annotated with the glycaemic state (ie, hypoglycaemic, normal, hyperglycaemic) according to the thresholds defined in table 1. Due to the lower sample frequency of the CGM, we will perform linear interpolation to estimate glucose measurements at every second.

**Table 1 T1:** Glycaemic event thresholds for people with T1DM^51–57^

Glycaemic event	Blood glucose concentration (mmol/L)
Severe hypoglycaemia	<2.8
Hypoglycaemia	>2.8 and <3.9
Euglycaemia	>3.9 and <11.1
Hyperglycaemia	>11.1 and <13.9
Severe hyperglycaemia	>13.9

T1DM, type 1 diabetes mellitus.

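### An unknown share of hypoglycaemic excerpts may follow a response to the low, so pooled sensitivity may overstate detection of lows not yet noticed

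*Protocol article*

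**What the plan says.** The reference glucose comes from a flash sensor: "Continuous glucose levels will be measured using a FreeStyle Libre 2 flash glucose monitoring system" (Protocol article, Continuous glucose monitoring). The same section says that "data will be extracted at regular intervals using a smartphone preconfigured with the companion application". The Discussion makes this the participant's task in free-living: "participants will be required to extract data from the CGM at least once every 8 hours". The reason given is storage: "The sensor can store data for a period of 8 hours". The Discussion treats scanning only as a source of missing data. In phase 1, "finger-prick blood samples will be taken periodically for capillary glucose measurements" (Calorimetry room).

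Under Data processing, heartbeats are grouped into excerpts and "annotated with the glycaemic state (ie, hypoglycaemic, normal, hyperglycaemic) according to the thresholds defined in table 1". Nothing in the labelling refers to when a low was seen or responded to. Data modelling and the Discussion add activity, mealtimes, meal composition and sleep as model inputs, and Data modelling plans subject-wise cross-validation. Covariates says that the recorded mealtimes, exercise and sleep allow periods such as the time after a meal to be analysed separately.

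**The concern.** The Introduction motivates the detector by lows that occur in sleep and go unnoticed. The performance figure that matters most is therefore sensitivity before anyone has reacted.

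When a participant reads a low value, or feels one, that person may wake, change posture, stop an activity or eat. Each can alter heart rate, heart rate variability and the activity signal. While glucose is still below the threshold, those excerpts keep the same label as excerpts from before the reaction. The label is correct. The difficulty is that the features then mix the effect of low glucose with the effect of the response to it.

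The planned mealtime and activity inputs open a second route, because food taken to correct a low can become a predictor of that low. Subject-wise cross-validation guards against learning individuals, but it does not guard against a behaviour that recurs in held-out participants.

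**Working it through.** **The article's own figure.** Sample size states 108 hours per participant with full participation: 36 + 3 × 24 = 108, which reproduces. The article gives no expected number or length of hypoglycaemic episodes and no actual scan frequency, so the share of hypoglycaemic time after a response can only be bounded by assumption.

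**Inputs from the article.**
- Maximum scan interval: 8 h = 480 min (Discussion), so at least 72/8 = 9 scans in three days.
- Sensor output: "the glucose concentration is reported in 15-minute intervals", so 72 × 4 = 288 readings in three days.

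**Assumed inputs.**
- Episode length D: 15 to 120 min.
- Scan intervals I shorter than 480 min.
- Evenly spaced scans that are unrelated to lows, with every scan during a low followed by a response.
- Sensitivity of 0.50 before and 0.90 after a response.

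**Formulas.** If an episode starts at random between scans, the wait to the next scan is uniform on 0 to I.
- Probability that an episode contains a scan: min(1, D/I).
- Expected share s of episode time after the first scan: D/(2I) if D ≤ I, otherwise 1 − I/(2D).
- Pooled sensitivity: 0.50(1 − s) + 0.90s = 0.50 + 0.40s. The overstatement is 0.40s.

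A simulation of the first two quantities agreed with the formulas.

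**At the 8-hour minimum (I = 480).**

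| D (min) | Episodes with a scan | Share s after scan |
|---|---|---|
| 15 | 3.1% | 1.6% |
| 30 | 6.3% | 3.1% |
| 60 | 12.5% | 6.3% |
| 120 | 25% | 12.5% |

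**For a 60-minute episode, with more frequent scanning assumed.**

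| Scan interval | Share s | Pooled sensitivity | Overstatement |
|---|---|---|---|
| 8 h | 60/960 = 6.25% | 0.525 | 0.025 |
| 4 h | 60/480 = 12.5% | 0.55 | 0.05 |
| 2 h | 60/240 = 25% | 0.60 | 0.10 |
| 1 h | 60/120 = 50% | 0.70 | 0.20 |

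These figures count scans only. Finger-pricks and responses to symptoms would add to the share. Scans that led to no reaction, and lows slept through, would reduce it.

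**The case against.** The strongest objection is that the only stated interval points to a small effect. The 8-hour rule is set by sensor storage, and at that interval about 6% of a 60-minute episode follows a scan. The Introduction also places hypoglycaemia typically in sleep, when voluntary scanning is least likely. This stands against any claim that such excerpts are common. It does not show that they are rare, because 8 hours is a minimum requirement and not an expected frequency, and symptoms may prompt a scan or a response.

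Second, eating, waking and finger-pricks are not confined to lows. Phase 1 has scheduled meals and exercise and periodic finger-pricks, and in phase 2 "the participants are free to go about their normal daily activities without restriction" (Study setting). A detector keyed to such events would raise false alarms and lose specificity. A reader might infer that the reaction is largely absent from non-hypoglycaemic time, and the article does not support that. The confounding is limited by this but not removed, since a reaction can still be more frequent during lows.

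Third, the article does not say who sees the values. Display to participants is a reasonable inference in free-living, where they operate the app. For staff in phase 1 it is weaker. The full protocol may settle this, so silence on masking is not itself the fault.

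Fourth, there is a partial safeguard. Activity and posture are recorded at 1 Hz (ECG), and Covariates allows analysis after meals. That does not separate eating that precedes a glucose change from eating that answers one. The activity diary, which includes food, is completed at the end of the day (Free-living), which weakens its timing.

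**Conclusion.** The concern holds as a possible bias of unknown size. Labels depend on glucose alone, participants read their own sensor, behavioural inputs enter the model, and the stated validation cannot reveal a response shared across participants. Pooled sensitivity may therefore be too high for the lows that the detector is meant to find.

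For 60-minute episodes and the assumed sensitivities, the overstatement runs from about 0.03 at the 8-hour minimum to 0.20 with hourly scans. Episode length, scan frequency above the minimum and both sensitivities are assumptions.

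A reader might infer that many hypoglycaemic excerpts will follow a seen low, and that a true 0.50 would be reported as, say, 0.74. That needs s = 0.60, which for a 60-minute episode means scans about every 48 minutes (1 − 48/120 = 0.60). The article states no such frequency. The point warrants a stratified report and does not call for a change of design.

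**What to change.** Leave clinical care and the display of glucose as they are, and change only what is retained and reported:

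- Keep the times of CGM scans, finger-pricks and recorded intake with the analysis data.
- In each hypoglycaemic episode, mark the first scan, finger-prick or recorded response. Alongside the pooled result, report sensitivity separately for excerpts before and after it, with the number of excerpts and episodes in each stratum.
- Flag excerpts around finger-pricks in both the hypoglycaemic and the non-hypoglycaemic class.
- Report the models with and without mealtime and activity inputs.

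The cost is retained time stamps, one stratified analysis and one further model comparison. Each stratum will hold fewer positive excerpts and have wider intervals, which matters because Sample size says that the number of episodes cannot be anticipated. For that reason the earlier stratum is proposed beside the pooled figure and not in its place. Responses to symptoms that nobody recorded will remain unseparated, and this should be stated as a limitation.

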### Ethics and dissemination

This study has received ethical approval from the Research Ethics Service (ref: 17/NW/0277). It is anticipated that the scientific findings of the study will be disseminated via presentation at national or international conferences and through publication in peer-reviewed scientific journals.
